### Interventions

After diagnosis of CRC, patients can be informed and included in PLCRC. If a patient gives informed consent, their PLCRC key study number is matched with their key number in the Netherlands Cancer Registry (NCR). PROMs are collected with questionnaires. PLCRC sends out these questionnaires at predefined time points from the moment of inclusion in PLCRC. For this study, specific questionnaires are added to the package of questionnaires to assess a possible difference in PROMs between condition A and condition B.

Prior to inclusion, patients have already received 12 months of follow-up care after their curative surgical resection. At the 12-month time-point, patients will undergo a diagnostic CT thorax-abdomen, colonoscopy and CEA measurement according to the current guideline. These results will be discussed at an outpatient clinic visit and will serve as baseline data for this study. This outpatient clinic visit will also be the start of the study for patients. Patients can still be included in PLCRC at this visit. According to the condition of the participating centre at the time of inclusion (A or B), a patient’s follow-up trajectory will differ corresponding to that condition.

#### In-hospital, standard-of-care follow-up (condition A)

Between 12 and 24 months after curative surgical resection, patients in follow-up under condition A will receive follow-up according to the current standard-of-care follow-up schedule in the participating centre. It is possible that this follow-up schedule deviates slightly from the national guideline.

#### Patient-led, home-based follow-up (condition B)

Before or during their outpatient clinic visit at 12 months after curative surgical resection, patients who will receive follow-up under condition B will receive written information on the PHFU. The treating physician/nurse practitioner will educate the participant on the PHFU and consecutively start the PHFU. If patients are not eligible for PHFU, they will receive in-hospital follow-up.

Participants will have their blood samples for the CEA measurement drawn at their general practitioner, the local diagnostic laboratory or the hospital. Preferably, patients will have their blood samples drawn as close to home as possible.

In principle, participants will receive notification by (e-)mail or text-message that they will have to perform their blood sampling for the CEA measurement. Reminders will be sent when the patient has missed the CEA measurement.

The patient will evaluate their own CEA level through the online patient platform portraying their test results. If the CEA level is normal, the participant is instructed not to act. If the CEA level is abnormal or the participant experiences symptoms, the participant is instructed to seek contact with their treating physician/nurse practitioner. If the participant does not seek contact with their treating physician/nurse practitioner, but the treating physician/nurse practitioner notices an abnormal CEA level, the participant will be contacted. Due to this construction, abnormal CEA levels will always lead to contact between patient and the treating physician/nurse practitioner. This construction is visualised in Fig. 2. If a participant wants to plan an outpatient clinic visit, they can always contact their treating physician/nurse practitioner – even if their CEA levels are normal.

**Fig. 2 Fig2:**
[figure not shown]
Flowchart of contact between participant and health care provider during patient-led, home-based follow-up. CEA; carcinoembryonic antigen. TP; treating physician. NP; nurse practitioner

At 24 months after start of the follow-up, a telephone consultation is planned. During this regular telephone consultation, the treating physician/nurse practitioner communicates the CEA level to the participant, and consults if the participant has any symptoms or questions. When the regular contents of the consultation have been addressed, the treating physician/nurse practitioner asks the participant the question: “Are you satisfied with the patient-led, home-based follow-up?” If a participant addresses clear objections to the PHFU, the remainder of the CRC follow-up for this participant will consist of in-hospital, standard-of-care follow-up. Otherwise, the PHFU is continued. A graphical representation of the protocol for the telephone consultation at 24 months after start of the follow-up (i.e., 12 months after inclusion in the study) has been added as Fig. 3.

**Fig. 3 Fig3:**
[figure not shown]
Protocol for telephone consultation at end of study. CEA; carcinoembryonic antigen

### Outcomes

#### Primary outcome

The primary outcome will be the proportion of participants who had contact with the hospital regarding CRC follow-up between 12 and 24 months after curative surgical resection. This endpoint will be compared between participants included under condition A and condition B.

#### Secondary outcomes

The secondary outcomes resulting from questionnaire data will be measured at 12 months after curative surgical resection (baseline), 18 months (6 months after inclusion) and 24 months (12 months after inclusion, end of study). The following secondary outcomes result from questionnaire data:HRQoL, measured by the European Organisation for Research and Treatment of Cancer Quality of Life (EORTC QLQ-C30) Questionnaire;Fear of cancer recurrence, measured by the Cancer Worry Scale (CWS) questionnaire;Anxiety, depression and distress, measured by the Hospital Anxiety and Depression Scale (HADS) questionnaire;Utility measure, measured by the EuroQol 5-Dimension 5-Level (EQ-5D-5L) questionnaire;Extramural costs, measured by a selection of relevant questions from the Medical Consumption Questionnaire (iMCQ) from the institute of Medical Technology Assessment;Productivity losses, measured by the Work Ability Index (WAI) questionnaire.

The following secondary outcomes result from other data than questionnaire data, and will be measured over the total study period:Cost-effectiveness, evaluated by integration of the questionnaire data and data extracted from the electronic patient records;OS, evaluated by data on vital status from the NCR; andCancer-specific survival, evaluated by data from the NCR on vital status and electronic patient records.

All abovementioned parameters will be compared between patients included under condition A and condition B.

#### Other variables

The following other variables will be collected from the electronic patient files and the NCR:Age at diagnosis;Date of resection;Date of inclusion;Centre of inclusion;Follow-up condition of centre at moment of inclusion (A or B);Participation in PHFU (yes or no);Sex (male or female);Localisation of primary tumour (according to the 3^th^ edition of the International Classication of Diseases for Oncology);Clinical and pathological TNM classification (according to the 8^th^ edition of the TNM classification);Type of surgical procedure (e.g., hemicolectomy, low anterior resection, etc.);Systemic/radiation treatment;Number of relevant comorbidities (according to the Charlson Comborbidity Index);CEA measurements; andMedical imaging reports.

### Participant timeline

This study starts 12 months after curative surgical resection. At this moment, CRC follow-up includes a diagnostic CT thorax-abdomen, colonoscopy, a CEA measurement with the results discussed in an outpatient clinic visit. Only patients who are disease-free at 12 months after curative surgical resection, are eligible for inclusion. Patients receive follow-up care according to condition of the hospital (A or B).

#### In-hospital, standard-of-care follow-up (condition A)

Participants who are included under condition A, will receive the current standard-of-care follow-up of the participating centre. It is possible that this current follow-up schedule deviates slightly from the current national guideline.

#### Patient-led, home-based follow-up (condition B)

Participants who are included under condition B, will receive the following follow-up care between 12 and 24 months after curative surgical resection, according to the PHFU care schedule:CEA measurement every three to six months (according to the national guideline);Outpatient clinic visit/telephone consult when requested by patient or treating physician/nurse practitioner.

The treating physician/nurse practitioner will seek contact with the patient in the following situations:The patient has abnormal CEA levels; orThe patient has not performed a CEA measurement within one month of the proposed check-up date.

The treating physician/nurse practitioner will request an in-hospital outpatient clinic visit in the following situations only:The patient has reported symptoms;The patient has an abnormal CEA level according to the national guideline.

The patient can seek contact with their treating physician/nurse practitioner at any time. The patient can also request an in-hospital outpatient clinic visit with their treating physician/nurse practitioner at any time.

#### Deviation from patient-led, home-based follow-up

After the centre has switched to condition B, PHFU is the new standard-of-care in a participating centre. For significant personal reasons, it is possible to deviate from PHFU and to provide the patient with the in-hospital, standard-of-care follow-up. Clear notation of the reason for the deviation needs to be documented in the electronic patient file of this patient. Patients who deviate from the condition of the participating centre but do meet the eligibility criteria, will be analysed following the intention-to-treat principle.

If a patient does not fit in the regular in-hospital follow-up at 12 months after curative surgical resection because of medical reasons, the patient meets an exclusion criterium and can therefore not be included in the study.

#### After the study

When participants reach the end of the study period, they will in principle receive PHFU for the remainder of their CRC follow-up. Also, patients will receive a colonoscopy following the Dutch guideline on endoscopic surveillance, three years after having received their first surveillance colonoscopy. Outpatient clinic visits are only performed when requested by the patient or the treating physician/nurse practitioner.

#### Questionnaires

Participants receive different questionnaires. Depending on the preference of participants, questionnaires are sent out either digitally or by mail. Participants receive these questionnaires from PLCRC following a predefined schedule. This schedule is as follows:Three, six, 12, 18, 24 months after inclusion in PLCRC;After 24 months, every 12 months.

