**Methods:**

This study is designed as a stepped-wedge cluster-randomised trial (SW-CRT) in six participating centres. During the trial, three centres will implement PHFU after six months; the other three centres will implement PHFU after 12 months of inclusion in the control group. Eligible patients are those with pT2-4N0M0 or pT1-4N1-2M0 CRC, who are 18 years or older and have been free of disease for 12 months after curative surgical resection. The studied intervention is PHFU, starting 12 months after curative resection. The in-hospital, standard-of-care follow-up currently implemented in the participating centres functions as the comparator. The proportion of patients who had contact with the hospital regarding CRC follow-up between 12–24 months after curative surgical resection is the primary endpoint of this study. Quality of life, fear of cancer recurrence, patient satisfaction, cost-effectiveness and survival are the secondary endpoints.

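### Questionnaires are sent by time since PLCRC inclusion, but the outcomes they carry are due by time since resection, and the article does not reconcile the two clocks

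*Protocol article*

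**What the plan says.** The Secondary outcomes section of the protocol article states that the questionnaire outcomes (QLQ-C30, CWS, HADS, EQ-5D-5L, iMCQ items, WAI) "will be measured at 12 months after curative surgical resection (baseline), 18 months (6 months after inclusion) and 24 months". In that sentence, inclusion means entry to the trial, which is the 12-month visit.

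The Questionnaires section gives the send dates as "Three, six, 12, 18, 24 months after inclusion in PLCRC" and then "After 24 months, every 12 months". Here inclusion means entry to the PLCRC cohort. The Interventions section repeats that anchor: "PLCRC sends out these questionnaires at predefined time points from the moment of inclusion in PLCRC". It also says how the trial's instruments reach patients: "specific questionnaires are added to the package of questionnaires to assess a possible difference in PROMs". No separate dispatch for this trial is described.

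Entry to PLCRC is spread over a long interval. The Recruitment section places the request around diagnosis and keeps it open until the outpatient visit 12 months after resection. The Interventions section agrees: "Patients can still be included in PLCRC at this visit".

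On satisfaction, the Methods paragraph of the abstract says: "Quality of life, fear of cancer recurrence, patient satisfaction, cost-effectiveness and survival are the secondary endpoints". The list under Secondary outcomes contains no satisfaction measure.

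**The concern.** One set of questionnaires has two start dates. The outcomes count from resection and the mailings count from PLCRC entry, while the gap between those dates differs from patient to patient. Followed literally, the send rule gives some patients no 12-month value, some no 24-month value, and some values displaced by up to several months.

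Two things are at stake. The first is the comparison of patient-reported outcomes between conditions. A nominal baseline completed after the 12-month visit has been answered while the assigned follow-up is already running. The second is the economic evaluation. Its QALYs come from the EQ-5D-5L in the same packages, over a 12-month horizon, with covariate adjustment planned for baseline differences. That calculation needs a utility at both ends of the horizon.

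The satisfaction endpoint is a separate mismatch in the same part of the plan. It has a different cause and a different remedy.

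**Working it through.** The plan gives no figure of its own on this point to reproduce. Its 360-patient total does not enter the check.

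**Inputs**
- Required times after resection: 12, 18, 24 months (Secondary outcomes).
- Send times after PLCRC entry: 3, 6, 12, 18, 24, then yearly, so next at 36 (Questionnaires).
- Latest PLCRC entry: the 12-month visit (Interventions; Recruitment).
- Earliest usual entry: around diagnosis. The interval from there to resection is not given, so every entry time below other than +12 is an assumption.

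**Formula.** Let s be the month of PLCRC entry relative to resection, negative if before it. Questionnaires then fall at s+3, s+6, s+12, s+18, s+24 and s+36 months after resection.

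**Exact agreement.** All three required times are met only if 12−s, 18−s and 24−s are all send times. That needs three send times spaced six months apart. The list holds two such triples: 12, 18, 24 (s = 0) and 6, 12, 18 (s = +6). No other entry time gives an exact match.

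**Other entry times.** Offsets are months from the nearest questionnaire to 12 / 18 / 24.

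| s (months) | Basis | Questionnaires, months after resection | Offsets |
|---|---|---|---|
| +12 | stated in the article | 15, 18, 24, 30 | +3 / 0 / 0 |
| +6 | assumed | 9, 12, 18, 24 | 0 / 0 / 0 |
| +2 | assumed | 14, 20, 26 | +2 / +2 / +2 |
| 0 | assumed | 12, 18, 24 | 0 / 0 / 0 |
| −1 | assumed | 11, 17, 23 | −1 / −1 / −1 |
| −3 | assumed | 9, 15, 21, 33 | 3 / 3 / 3 |
| −4 | assumed | 14, 20, 32 | +2 / +2 / −4 |
| −6 | assumed | 12, 18, 30 | 0 / 0 / 6 |

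At s = +12 the first questionnaire arrives three months into the assigned condition, so the listed schedule supplies no baseline. The 18- and 24-month values are on time because trial entry and PLCRC entry are then the same day. At s = −6 the 24-month value is absent; the nearest are six months either side, at 18 and 30. At s = +2 the nominal baseline falls two months after follow-up under the condition began.

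**Tolerance.** The article states no window. With an assumed ±1 month, all three assessments fit for s from −1 to 1 or from 5 to 7. With ±2 months they fit for s from −2 to 2, 4 to 8, or 10 to 11, although some of the accepted baselines would then fall after the 12-month visit.

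**QALY.** The horizon runs from month 12 to month 24. Entry at +12 lacks the utility at its start. Entry at −6 lacks the utility at its end, which could only be interpolated using a value six months beyond the horizon.

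**Satisfaction, passages side by side.** The abstract names it as a secondary endpoint; the outcome list has no instrument for it. The only satisfaction question is in the description of condition B. The treating clinician asks it in the 24-month telephone consultation, and it concerns the home-based follow-up itself. It therefore has no counterpart under condition A.

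**The case against.** **The cohort has its own documentation.** The article condenses PLCRC's schedule, and a questionnaire at enrolment may exist without being listed. If so, a patient joining at the 12-month visit would have a baseline. This stands as a limit on that one case. It does not help the assumed entries at −6, −3 or +2. The absence of windows or mapping rules is likewise no fault, since those belong in an analysis plan. The finding is that two stated schedules conflict.

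**Many patients may be unaffected.** Entry at resection or six months later is exact, and entry within about a month of resection is off by a month at most. A reader might infer that a large share of the trial is mistimed. The documents do not support that, because they give no distribution of entry times.

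**The model tolerates irregular data.** Patient-reported outcomes go into a linear mixed model with hospital and patient random effects. It does not require complete baselines or identical times, and the article plans no baseline-to-24-month contrast. This is fair, provided that actual timing enters the model. The QALY calculation is less forgiving.

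**Bias between conditions.** A reader might infer that missing baselines favour one condition, because late joiners enter when the centre's condition is in force and nobody is blinded. The article allows late joining under both conditions and gives no sign that its frequency differs. This remains a possibility, not a result.

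**Conclusion.** The point holds as an unreconciled time anchor and should be fixed. The send schedule as written cannot deliver the stated 12-, 18- and 24-month assessments except for entry at resection or six months after it. For a patient entering at the 12-month visit, a route that the article expressly allows, it yields no baseline unless PLCRC issues an unlisted questionnaire at enrolment. Under the assumed entry times the errors run from one month (s = −1) to a missing end-of-study value (s = −6).

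The number of patients concerned cannot be stated. The exposed results are the questionnaire-based secondary outcomes, the questionnaire inputs to costs, the 12-month QALY and its baseline adjustment. The primary outcome is hospital contact and does not come from questionnaires. Survival comes from the cancer registry and patient records. Neither is touched, and nor is the sample size.

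The satisfaction mismatch also holds, as a separate and smaller matter: as described, it can be reported for condition B but not compared.

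**What to change.** Trigger the trial's questionnaire package at 12, 18 and 24 months from the date of resection, which the Other variables section already lists for collection. Send the 12-month package before the 12-month visit. The scheduled offset is then zero whatever the PLCRC entry date. Patients who join PLCRC only at that visit cannot be mailed beforehand and would need the package on the day.

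Inclusion began in July 2022, so some questionnaires will have gone out on the existing schedule. Analyse these by actual months since resection, and do not treat one completed after the assigned follow-up has started as a baseline. Baselines that were never collected cannot be recovered.

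The cost is a separate send rule in PLCRC and a few extra mailings. PLCRC serves several studies, and the article does not show whether a study-specific rule is already available, so this should be checked with the cohort.

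For satisfaction, add one item to the 24-month package for both conditions, or drop it as a compared endpoint and bring the abstract into line with the outcome list.

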### Sample size

In this SW-CRT, it is expected that the primary endpoint, the proportion of patients who had contact with the hospital regarding CRC follow-up care within the 12 months follow-up period, is approximately 100% in the in-hospital, standard of care follow-up and approximately 40% during the PHFU.

Over a realistic range of assumptions, this design has at least 80% power to detect a meaningful difference in the proportions of patients contacting the hospital. Specifically, this is the case:If at least 20 patients per six months per hospital can be included in the DISTANCE trial;If the hospital intra cluster coefficient (ICC) of the primary outcome is no more than 0.20 (typical hospital ICC are around 0.05–0.10) [12]; andIf the difference between the primary outcome in condition A and condition B is more than 40% (expected difference based on implementation in Radboud university medical center: 70%).

Of note, if 20 patients per hospital per half year will be included, then the total number of patients will be 360. Of these 360 patients, 180 will be included under condition A and 180 will be included under condition B.

### Recruitment

Around diagnosis, CRC patients are asked to be included in PLCRC by their treating physician. Patients can give their informed consent for different aspects of PLCRC (use of medical data, PROM questionnaires, additional blood samples, new studies, and information on diagnostic coincidence findings). One of the major advantages of PLCRC is that when patients have given their informed consent for PLCRC, they can participate in all studies that make use of the PLCRC infrastructure. During the outpatient clinic visit at 12 months after curative surgical resection, patients can still be recruited for and included in PLCRC.

Patients do not have a choice whether or not they are included in the in-hospital, standard of care follow-up or the PHFU; this is decided by the condition in which the participating centre is at the moment of inclusion. Once PHFU is implemented in a participating centre, this is the new standard of care for all CRC patients in follow-up in that centre. Only patients who are included in PLCRC, are eligible to be analysed in this study. Informed consent for this study specifically is not necessary.

Eligible patients are automatically included in this study. The principal investigator of the participating centre will keep track of the patients who are included in the study.

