### Allocation of switch moment

Follow-up care will be provided according to the current follow-up condition of the participating centre. For three of the six participating centres, this switch to including patients under condition B will occur after six months of including patients under condition A. For the other three participating centres, the switch to condition B will occur after 12 months of including patients under condition A.

The moment of switching will be allocated using a simple randomisation based on a single sequence. The randomisation will be performed between the six participating centres before the start of inclusion by the study coordinator and the project leader.

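### One sentence in Recruitment conflicts with the rule that care is fixed at inclusion; because nearly every control window crosses its hospital's switch, a hospital applying that sentence would contaminate its controls

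*Protocol article*

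**What the plan says.** Two rules for a participant's care stand side by side in the protocol article.

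**Care fixed at inclusion.** On whether a patient gets in-hospital follow-up or PHFU, Recruitment says "this is decided by the condition in which the participating centre is at the moment of inclusion". Interventions ties the follow-up trajectory to the hospital's condition at the time of inclusion. Its condition A subsection covers the whole window: "Between 12 and 24 months after curative surgical resection, patients in follow-up under condition A will receive follow-up". Participant timeline describes condition B care for those included under B. After the study moves participants to PHFU when their study period ends. The abstract adds: "The studied intervention is PHFU, starting 12 months after curative resection".

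**Care follows the hospital's present state.** The next sentence of Recruitment reads "Once PHFU is implemented in a participating centre, this is the new standard of care for all CRC patients in follow-up in that centre". Allocation of switch moment opens with a weaker echo, "Follow-up care will be provided according to the current follow-up condition of the participating centre", but then describes the event, for the early hospitals, in terms of inclusion: "this switch to including patients under condition B will occur after six months of including patients under condition A". The section on deviation from PHFU says "After the centre has switched to condition B, PHFU is the new standard-of-care in a participating centre", which fits either rule.

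No sentence says outright what happens to a condition A participant who is still in follow-up when the hospital switches. Study setting rules out a transition period.

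**The concern.** A condition A participant 15 months after resection is a colorectal cancer patient in follow-up. Taken at its word, the broad sentence puts that person on PHFU on the day the hospital switches. The analysis would still count the person as A, because Primary outcome compares participants by the condition they were included under and the deviation section specifies intention-to-treat.

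The part of the control window after the move would then look like the intervention. The patient-reported and cost contrasts would shrink towards zero. For the patient-reported outcomes this is the harmful direction, because a null difference would be read as reassurance that PHFU does no harm to quality of life or fear of recurrence. The primary contact contrast could also shrink, though less surely.

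**Working it through.** **Inputs.** From Sample size: 20 patients per hospital per six months, contact rates of about 100% (A) and 40% (B). From Study setting: three hospitals switch at month 6 and three at month 12, with no transition. From Background: each participant is followed from 12 to 24 months after resection, a 12-month window. Even accrual is my assumption.

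**The plan's own figure.** 6 hospitals × 3 half-years × 20 = 360. Condition A: 3 × 1 × 20 + 3 × 2 × 20 = 60 + 120 = 180. Condition B: 120 + 60 = 180. This matches the article.

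**Do control windows cross the switch?**
- Early hospitals: controls enter in months 0–6 and finish in months 12–18. The switch is at month 6, so all cross it.
- Late hospitals: controls enter in months 0–12 and finish in months 12–24. The switch is at month 12, so all cross it except a patient included on the very first day.

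**Control months after the switch.**
- Early, entering on average at month 3: 15 − 6 = 9 of 12 (75%).
- Late, first half-year, entering on average at month 3: 15 − 12 = 3 of 12.
- Late, second half-year, entering on average at month 9: 21 − 12 = 9 of 12. The late hospitals average 6 of 12 (50%).
- Overall: (60 × 9 + 60 × 3 + 60 × 9) / 180 = 7 of 12 (58%).

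Under the inclusion rule, none of these months is spent on PHFU.

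**Patient-reported outcomes, if all six hospitals applied the broad sentence.** Secondary outcomes puts the questionnaires 6 and 12 months after inclusion.
- 6 months: early controls answer in months 6–12 (after the switch), late first-half controls in months 6–12 (before), late second-half controls in months 12–18 (after). Past the switch: 60 + 60 = 120 of 180 (67%).
- 12 months: 180 of 180.

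**Costs, accrued evenly, moved participants costing the same as PHFU.** Share of the crude contrast kept:
- all six hospitals: 1 − 7/12 = 42%
- one early hospital: (160 + 20 × 0.25) / 180 = 92%
- one late hospital: (140 + 40 × 0.50) / 180 = 89%

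**Primary endpoint, illustration only.** The article gives no visit schedule for condition A. I assume the first in-hospital contact comes 3 or 6 months after inclusion, borrowing the CEA interval in Background, and a 40% contact rate for anyone moved before it.
- 3 months, all six: half of the 60 early controls and a quarter of the 120 late controls have no earlier contact, 30 + 30 = 60. A = (120 + 60 × 0.40) / 180 = 80%; the crude difference falls from 60 to 40 points.
- 6 months, all six: 60 + 60 = 120 have none. A = (60 + 120 × 0.40) / 180 = 60%; the crude difference is 20 points.
- If the move itself counts as a contact, the difference stays at 60 in both cases.
- The planned model adjusts for recruitment period, so its estimate can differ from the crude one. Take one late hospital and 3 months: 10 of its 40 controls are affected, so crude A = (170 + 10 × 0.40) / 180 = 97%, a difference of 57. The adjusted estimate rests on the middle period, the only one with both conditions: late hospitals average (1 + 1 + 0.70) / 3 = 90% against 40%, a difference of 50.

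**The case against.** The case for leaving the text alone is strong, and most of it stands.

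- The broad sentence cannot be meant literally. PHFU starts only at 12 months after resection, ineligible patients stay in hospital follow-up, and personal reasons allow deviation. The sentences that follow it concern who is analysed and whether study-specific consent is needed, so its universal wording may simply mean patients inside and outside the PLCRC cohort.
- The opening of Allocation of switch moment is qualified by its own next sentence. The conflict therefore rests mainly on one sentence.
- Since every control window crosses the switch, the literal rule would leave the move described in After the study with nothing to do for condition A participants. Interventions describes PHFU starting around the 12-month visit and no mid-window start.
- The article condenses a fuller protocol, which may instruct hospitals on patients already in follow-up.

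A reader might infer that the protocol orders controls to cross over, that the trial's controls are contaminated, or that the primary contrast could be lost or reversed. The documents support none of these. The weight of the text is against crossover, nothing shows that any hospital moved anyone, and the primary-endpoint figures depend on visit timing, on a 40% rate applied to partial windows, and on whether the move is a countable contact.

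What remains is not an omitted detail. The article states a care rule that disagrees with the sentence before it, on a matter that six hospitals must act on, and the broad sentence is the one a clinic would naturally apply when it changes its standard of care.

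**Conclusion.** The inconsistency is real and worth correcting, but it is conditional. On the better-supported reading the effect is zero. It becomes material only in a hospital that applied the broad sentence to participants already included under A. If all six did, 58% of control follow-up would fall after the switch, about 42% of the cost contrast would remain, and two thirds of controls at 18 months and all at 24 months would be measured past the switch. If one hospital did, about 89–92% of the cost contrast would remain.

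These sizes assume even accrual at 20 per hospital per half-year and, for costs, even accrual over the window. The questionnaire counts are of participants, not of returned forms: questionnaires are optional and, according to Questionnaires, are scheduled from PLCRC inclusion. Any effect on the primary endpoint lies between none and substantial, and the article does not allow it to be pinned down.

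**What to change.** **Text.** In Recruitment, limit the sentence to patients who reach their 12-month visit after the hospital's switch. Add that participants included under condition A stay on in-hospital follow-up until 24 months after resection, whatever the switch date. Align the opening of Allocation of switch moment and the sentence in the deviation section.

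**Check.** Inclusion began in July 2022, so ask each of the six hospitals which rule it has applied. Record the date of any move before month 24: Other variables lists PHFU participation only as yes or no. The switch date is a fair proxy only if a hospital moved everyone at once.

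**Analysis.** Keep intention-to-treat by condition at inclusion. Only if moves occurred, state whether the contact that starts PHFU counts towards the primary endpoint, and consider a supplementary analysis censoring A participants at the move. If none occurred, nothing more is needed.

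**Cost.** A clarifying clause in two or three places and six queries. Hospitals run both pathways in parallel for up to 12 months after switching, which the inclusion rule already implies. If some participants have moved, the expected contrasts must be restated less favourably.
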